### Objective

2.1

This study aims to explore acupuncture’s efficacy in post-stroke dysphagia (PSD) patients, clarify the neural mechanisms of acupuncture intervention for PSD, and obtain high-quality evidence.

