#### The healthy control group

2.8.3

At baseline, functional MRI will be conducted to assess Regional Homogeneity (ReHo) and Amplitude of Low-Frequency Fluctuations (ALFF), together with Fiberoptic Endoscopic Evaluation of Swallowing (FEES). The study will not involve additional interventions or follow-up assessments, as published evidence (22, 23) supports the 12-month stability (ICC ≥ 0.75) of these resting-state and swallowing-related fMRI metrics. Further MRI scans would entail unnecessary radiofrequency exposure and patient travel burden, offering no clinical benefit and contravening the minimal-risk ethical principle.

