##### Recovery of the swallowing center and peripheral nerves

2.9.2.1

(1) fMRI data acquisition and analysis

Functional magnetic resonance imaging (fMRI) will be acquired to measure ReHo and ALFF indicators, which will be assessed before and during treatment. The ReHo indicator quantifies local neural activity synchronization, with changes indicating functional reorganization at the regional level (28). The ALFF metric reflects spontaneous neural activity intensity, thereby indicating the dynamic changes in brain functional reorganization (29).

Structural images are obtained using a TI-3D MPRAGE sequence with a sagittal scan orientation (left-to-right acquisition), yielding high-resolution T1-weighted images of the whole brain. Scan parameters are: repetition time (TR)/echo time (TE) = 2,000 ms/1.97 ms; flip angle (FA) = 8°; number of excitations (NEX) = 0.5; field of view (FOV) = 256 × 256 mm; matrix size = 256 × 256; slice thickness = 1.0 mm; no gap; 192 slices; scan time = 4 min 40 s; total images = 190.

Resting-state fMRI (rs-fMRI) data are acquired using a gradient-echo (GRE) single-shot echo-planar imaging (EPI) sequence. Scan parameters are: TR/TE = 2,000 ms/30 ms; FA = 90°; FOV = 220 × 220 mm; matrix = 64 × 64; slice thickness = 3 mm; gap = 3 mm; 37 slices; 240 time points; scan time = 8 min 8 s; producing 2,037 volumes.

Functional MRI data will undergo a standardized preprocessing pipeline. First, DICOM images will be converted to NIfTI format, followed by the exclusion of participants exhibiting excessive head motion—defined as translation exceeding 2 mm or rotation > 2°—or signal artifacts. Subsequent core preprocessing will include realignment for motion correction, slice timing adjustment, spatial normalization to the MNI152 template at 2 mm^3^ isotropic resolution, nuisance regression incorporating six head motion parameters along with cerebrospinal fluid and white matter signals, and band-pass filtering between 0.01 and 0.08 Hz. Finally, spatial smoothing will be applied using a 6 mm full-width-at-half-maximum Gaussian kernel.

Regions of interest (ROIs) will be defined based on the Automated Anatomical Labeling (AAL) atlas (30). In accordance with previous neuroimaging studies on swallowing mechanisms (31), the ROIs will include the precentral gyrus, insula, and anterior cingulate cortex.

(2) Surface electromyography (sEMG) detection

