### Evaluation schedule

2.10

FOIS, NIHSS, SWAL-QOL, PAS, and YPR-SRS will be assessed at baseline (pre-treatment), 15 and 30 days after treatment initiation, and 30 and 60 days post-treatment completion. Additionally, fMRI-derived ReHo and ALFF metrics, sEMG evaluations, and PRO scores will be obtained at baseline and at 15 and 30 days following treatment initiation. The study timeline for enrollment, intervention, and assessment is detailed in Table 4. All dropouts and their respective reasons will be systematically documented in the case report forms (CRFs).

**TABLE 4 T4:** Study assessment schedule.

Times outcomes	Before treatment	Treatment				Follow-up	
	Day 3–0	Week 1–2	(Day 15)	Week 2–4	(Day 30)	Day 60	Day 90

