#### Functional imaging evaluation indicators

2.12.1

Statistical analysis is performed using the DPABI V5.1^3^ software package. Whole-Brain Analysis: Paired *t*-tests will be used to compare pre- and post-intervention ALFF, fALFF, ReHo, and FC values within each group (acupuncture and rehabilitation training), as well as between groups after intervention. Based on prior evidence indicating direction-specific neuromodulation by acupuncture in swallowing networks (47, 48), the resulting statistical maps will be corrected using one-tailed Gaussian random field theory (voxel *p* < 0.01, cluster *p* < 0.05). ROI Analysis: Mean ReHo and ALFF values will be extracted from each ROI and analyzed using repeated-measures ANOVA to assess within-group changes over time and between-group differences.

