#### Analysis of Deqi

2.12.4

Group comparisons will be performed based on the binary classification of “adequate” versus “inadequate” deqi, with the Deqi Quality Index (DQI) included as a covariate in an analysis of covariance (ANCOVA) to assess therapeutic effects. Additionally, a linear mixed-effects model will be employed to examine the significance of the DQI × time interaction.

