#### Statistical control for confounding factors

2.12.5

Potential confounders, including age, sex, PSD duration, baseline NIHSS and FOIS scores, stroke subtype, comorbidities (hypertension, diabetes), total treatment expectation scores, and the Deqi Index (DQI), will be accounted for in the analyses. For primary and secondary efficacy outcomes, repeated-measures mixed-effects models or multiple linear regression will be employed. Stroke subtypes will be examined using stratified analysis, while comorbidities will be assessed via sensitivity analyses.

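### The ROI analysis of ReHo and ALFF treats baseline as a repeated outcome and leaves its between-arm contrast undefined; a baseline-adjusted day-30 comparison would be clearer and usually more powerful

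*Protocol article*

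**What the plan says.** Section 2.1 makes mechanism part of the aim: "clarify the neural mechanisms of acupuncture intervention for PSD". The introduction sets the comparison against conventional swallowing rehabilitation.

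Section 2.9.2.1 lists ReHo and ALFF as secondary outcomes and fixes the regions: "the ROIs will include the precentral gyrus, insula, and anterior cingulate cortex". Section 2.10 fixes the visits: "fMRI-derived ReHo and ALFF metrics, sEMG evaluations, and PRO scores will be obtained at baseline and at 15 and 30 days following treatment initiation".

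Section 2.12.1 says the ROI means are "analyzed using repeated-measures ANOVA to assess within-group changes over time and between-group differences". It does not say which term of the ANOVA is the between-group comparison. In the same section, the whole-brain analysis compares "values within each group (acupuncture and rehabilitation training), as well as between groups after intervention".

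Two later sections bear on the point. Section 2.12.5 says: "For primary and secondary efficacy outcomes, repeated-measures mixed-effects models or multiple linear regression will be employed". It lists baseline NIHSS and FOIS among the covariates, but not the baseline ROI value, and states no arm-by-visit contrast. Section 2.12.4 contains the only interaction the article names: "a linear mixed-effects model will be employed to examine the significance of the DQI × time interaction". That concerns the deqi index, not the randomised arm.

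**The concern.** The mechanism question in a two-arm randomised trial is whether ReHo and ALFF change more with acupuncture than with rehabilitation. The ROI sentence gives two targets, and neither is stated as that contrast.

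- **Change within an arm.** Patients enter 15 to 180 days after stroke, and all receive standard stroke treatment. A change from baseline in the acupuncture arm mixes any acupuncture effect with recovery and background care.
- **Between-group differences.** This could mean the group main effect, which averages the arms over all three visits, including a baseline at which randomisation makes the expected difference zero. It could also mean the group-by-time interaction. The sentence does not settle which.

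At stake is how the imaging results will be read. A significant change in one arm and not in the other could be taken as an acupuncture-specific mechanism. Conversely, a real arm difference could be missed because the chosen term is diluted.

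**Working it through.** **Inputs from the article.** Three imaging visits (2.10); 40 evaluable patients per arm (2.7). The 40 is the FOIS figure and reproduces with a one-sided 5% level: 2 × (1.645 + 0.842)² × 1.09² / (1.31 − 0.31 − 0.39)² = 39.5, so 40 per arm; 40 / 0.8 = 50 per arm, 100 in total. The article states no power for the ROI analysis.

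**Assumptions, not in the article.** SD 1 at each visit; equal correlation r between visits, 0.5 or 0.75; true arm difference 0, 0.25 and 0.5 SD at baseline, day 15 and day 30; two-sided 5% tests.

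**Group main effect.**
- It estimates (0 + 0.25 + 0.5) / 3 = 0.25 SD, half the day-30 effect.
- Its standard error is √[(1 + 2r)/3 × 2/40].
- r = 0.5: 0.25 / 0.183 = 1.37, power 27%.
- r = 0.75: 0.25 / 0.204 = 1.22, power 23%.

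**Group-by-time.**
- Noncentrality is (40/2) × Σ(dⱼ − d̄)² / (1 − r), where dⱼ is the arm difference at visit j and d̄ its mean. Here Σ = 0.25² + 0² + 0.25² = 0.125.
- r = 0.5: 2.5 / 0.5 = 5, power about 49–50% on 2 and 156 degrees of freedom.
- r = 0.75: 2.5 / 0.25 = 10, power 81%.

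**Day 30 adjusted for baseline.**
- The standard error is √[(1 − r²) × 2/40].
- r = 0.5: 0.5 / 0.194 = 2.58, power 72%.
- r = 0.75: 0.5 / 0.148 = 3.38, power about 91–92%.

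A simulation of 10,000 trials per scenario gave 27% and 23%, 49% and 81%, and 72% and 91% in the same order. With 50 per arm the ranges were 27–33%, 60–89% and 81–96%. With no arm difference, all three tests rejected in about 5% of trials, so all three are valid.

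**Sensitivity to timing.** If the full 0.5 SD is already present at day 15, the main effect estimates 1/3 SD and Σ = 1/6.
- r = 0.5: power is about 44% (main effect), 62% (group-by-time) and 72% (adjusted day 30).
- r = 0.75: it is about 36%, 91% and 92%.

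The advantage over group-by-time therefore nearly vanishes when the effect appears early and the correlation is high. The advantage over the main effect remains in every case examined.

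**Change within an arm.** Suppose acupuncture adds nothing over rehabilitation, but both arms recover linearly by 0.3 SD at day 30 (assumed).
- Noncentrality is 40 × (0.15² + 0.15²) / (1 − r), that is 3.6 or 7.2. The time test in the acupuncture arm rejects in about 37% (r = 0.5) or 65% (r = 0.75) of trials.
- In the simulation the two arms disagreed on significance in 45–48% of these trials, although they did not differ.
- With 0.5 SD recovery, the time test rejects in about 80–98% of trials.

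**The case against.** The strongest reply is that the ROI sentence can be read favourably. It never mentions a main effect, and a two-group, three-visit ANOVA also produces the interaction. A reader might infer that the plan commits to the group main effect and so never tests the arms against each other. The article does not support that: the term is undefined, and even the main effect keeps its 5% level under randomisation and has some power. It is inefficient, not invalid.

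A reader might also take the within-arm rejection rates as inflated type I error. They are not. In those scenarios the arm mean really changes, so rejecting no change is correct. The error would lie in presenting it as an acupuncture-specific effect, and nothing in the article says that this will be done.

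The correlation of 0.75 deserves the same caution. The article says published evidence "supports the 12-month stability (ICC ≥ 0.75) of these resting-state and swallowing-related fMRI metrics", but uses this to justify not rescanning healthy controls. It is not a between-visit correlation for treated stroke patients, so 0.75 remains an assumption here.

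Two other provisions help only in part. The whole-brain analysis includes a post-intervention comparison between arms, but without baseline adjustment. Section 2.12.5 allows a mixed model for secondary outcomes, close to the model family proposed below, but names neither the baseline ROI value nor the arm-by-visit contrast, and is not reconciled with the ANOVA in 2.12.1.

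Finally, an analysis plan that is not shown could specify the contrast. That is fair as to the missing detail. What stands is that the article itself fixes a method that uses baseline as an outcome and gives change within an arm as one of its two targets.

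**Conclusion.** The point holds as a low-to-moderate improvement to a secondary mechanistic outcome. Within-arm change cannot isolate acupuncture; this is a matter of design and does not depend on any assumed figure. The between-group target is ambiguous. On the main-effect reading the test is valid but diluted; on the interaction reading it is sound but, in most scenarios examined, less powerful than adjusting day 30 for baseline.

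The size of the loss rests on the assumed effect, its time course, the correlation, and 40 usable scans per arm. That last figure is the FOIS target, and exclusions for head motion could lower it. The documents do not show that the ROI analysis fails to compare the arms, or that it will produce false claims. The primary outcome and the sample size are not affected.

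**What to change.** Replace the ROI sentence in 2.12.1 with wording such as: For each ROI, ReHo and ALFF at days 15 and 30 will be analysed with a linear mixed model including arm, visit, arm-by-visit and the baseline ROI value. The between-arm test is the baseline-adjusted arm difference at day 30. Within-arm changes over time are descriptive and will not be used as evidence of an acupuncture effect.

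If ANOVA is kept, name the group-by-time interaction as the between-arm test. In either case, state that this sentence, rather than the general model choice in 2.12.5, governs ROI ReHo and ALFF.

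The cost is a few sentences of analysis wording. The scans are already scheduled, and no patients or visits are added. The only thing given up is the use of within-arm p-values as evidence of mechanism.

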**Methods:**

This study is a multicenter, open-label, randomized clinical trial. A total of 115 participants will be enrolled: 100 PSD patients will be randomly allocated in a 1:1 ratio to the experimental group (acupuncture combined with basic treatment) or the control group (rehabilitation training combined with basic treatment), and 15 healthy controls will only provide baseline information without receiving any treatment. Both groups will be given a 4-week intervention (three times per week). The primary efficacy outcome measure is the Functional Oral Intake Scale (FOIS). Secondary outcome measures include: Regional Homogeneity (ReHo) and Amplitude of Low-Frequency Fluctuation (ALFF) metrics from Functional Magnetic Resonance Imaging (fMRI) scans, surface electromyography (sEMG) assessments, the Swallowing Disorders-Specific Quality of Life Questionnaire (SWAL-QOL), the National Institutes of Health Stroke Scale (NIHSS), the Treatment Expectation Questionnaire (TEX-Q) and patient-reported outcomes (PRO). Additionally, the Fiberoptic Endoscopic Evaluation of Swallowing (FEES) will be performed together with the Penetration-Aspiration Scale (PAS) and the Yale Pharyngeal Residue Severity Rating Scale (YPR-SRS). Outcomes will be assessed at five time points: Baseline, day 15 and day 30 during treatment, and 30 and 60 days after treatment. All primary analyses will be conducted using both intention-to-treat and per-protocol approaches.

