### Sample size, randomization, and blinding

2.7

The primary efficacy outcome is the FOIS score. As neither our team nor previous studies have used this measure to assess acupuncture efficacy for post-stroke dysphagia, it is not possible to determine an appropriate effect size from existing data. A review of similar studies has revealed that after 4 weeks, the FOIS score difference from baseline was 1.31 (rehabilitation training group) vs. 0.31 (sham training group), with a standard deviation of 1.09 (16). This value will be used as the expected effect size for this trial, and sample size calculations will be conducted based on a superiority trial design (17). These parameters (μA = 1.31, μB = 0.31, σ = 1.09, α = 0.05, power = 0.8, δ = 0.39) were applied in a superiority design with 1:1 allocation. After calculation, nA = nB = 40. Considering a 20% dropout rate, this study is expected to enroll 100 patients.

Randomization will use computer-generated numbers to allocate patients equally to acupuncture or rehabilitation groups. A stratified block randomization design will be employed. An independent statistician will generate all random sequences in SPSS 25.0, with study center and baseline FOIS as stratification factors, block lengths of 4 and 6 randomly interleaved, and the seed number set to 20240420. Allocation concealment will be implemented through sequentially numbered, opaque, sealed envelopes kept by a research coordinator who has no conflicts of interest with the study team. After participants have completed baseline assessments and provided written informed consent, the responsible physician will open the corresponding envelope on-site to reveal the allocation. The statistician generating the random sequence will operate independently of the coordinator handling allocation concealment. Neither patients nor physicians will know the allocation in advance. All participants will be followed for 90 days.

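### Repeated-measures ANOVA for the ROI imaging outcomes uses only patients with all three scans, and 2.12.5 names other methods for secondary outcomes; separately, the motion rule removes whole participants

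*Protocol article*

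**What the plan says.** The abstract of the protocol article gives ReHo and ALFF secondary status: "Secondary outcome measures include: Regional Homogeneity (ReHo) and Amplitude of Low-Frequency Fluctuation (ALFF) metrics". Section 2.10 fixes three scans: "fMRI-derived ReHo and ALFF metrics, sEMG evaluations, and PRO scores will be obtained at baseline and at 15 and 30 days following treatment initiation".

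For the regions of interest, section 2.12.1 states that mean ReHo and ALFF will be "analyzed using repeated-measures ANOVA to assess within-group changes over time and between-group differences". Section 2.12.5, on control of confounders, states: "For primary and secondary efficacy outcomes, repeated-measures mixed-effects models or multiple linear regression will be employed". Repeated-measures ANOVA is not among the methods named there.

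Two other places determine how many scans reach the analysis. The preprocessing text in section 2.9.2.1 converts the image format, "followed by the exclusion of participants exhibiting excessive head motion" (translation above 2 mm or rotation above 2°). The unit removed is the participant. Section 2.7 makes a dropout allowance for the FOIS sample size: "Considering a 20% dropout rate, this study is expected to enroll 100 patients". Section 2.5 lists deterioration, serious complications and poor compliance among the grounds for dropout.

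**The concern.** Standard repeated-measures ANOVA needs a value at every visit. A patient with good scans at baseline and day 15 but none at day 30 contributes nothing, although the two scans exist and could be used. Meanwhile 2.12.1 and 2.12.5 point to different methods for what appears to be the same outcome, so the analyst could choose between them after seeing the data.

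The motion rule is a second, separate loss. It acts at preprocessing, before any model is fitted, and takes out all of a participant's scans even if only one was spoiled.

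Clarifying the neural mechanism is a stated objective (section 2.1), and the ROI comparison serves it directly. The stakes are some precision, and the risk that a comparison of completers describes a selected group, because the grounds for dropout in 2.5 are partly related to how patients fare.

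**Working it through.** **The plan's own figure.** Inputs from section 2.7: "μA = 1.31, μB = 0.31, σ = 1.09, α = 0.05, power = 0.8, δ = 0.39". The effective difference is 1.31 − 0.31 − 0.39 = 0.61. With one-sided α = 0.05, n per arm = 2 × 1.09² × (1.645 + 0.842)² / 0.61² = 39.5, rounded up to 40. This matches "After calculation, nA = nB = 40". Dividing by 0.8 gives 50 per arm and 100 in total. The figures reproduce. They concern FOIS; the article gives no sample size for imaging.

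**Complete cases.** Let m be the chance that a scan is lost to motion, independently at each visit. The plan gives no value for m, so 5%, 10% and 20% are assumptions. Applying the 20% dropout to scans by day 30 is an inference. Patients per arm with all three scans usable = 50 × 0.8 × (1 − m)³:

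- m = 0: 40.0
- m = 5%: 34.3
- m = 10%: 29.2
- m = 20%: 20.5

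**Variance of the day-30 contrast.** The target is the between-arm difference in change from baseline to day 30. I assume equal variance σ² at each visit, a common within-patient correlation ρ, and half of the dropout before day 15. For n complete cases per arm, the variance is 2 × 2σ²(1 − ρ)/n. At ρ = 0.5 and n = 40 this is 4 × 0.5/40 = 0.050σ². The mixed-model variance comes from generalised least squares: sum the information from each pattern of observed scans, weighted by its expected frequency, invert, and read off the contrast. At ρ = 0.5 with dropout only it is 0.047σ², a ratio of 1.063.

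Ratio of complete-case to mixed-model variance when the motion rule removes only the affected scan:

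| m | ρ = 0.3 | ρ = 0.5 | ρ = 0.7 |
|---|---|---|---|
| 0 (dropout only) | 1.080 | 1.063 | 1.048 |
| 5% | 1.183 | 1.159 | 1.137 |
| 10% | 1.303 | 1.268 | 1.238 |
| 20% | 1.610 | 1.544 | 1.487 |

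**Which change produces the gain.** Now keep the participant-level motion rule and change only the model. The same calculation gives 1.06 to 1.07 at ρ = 0.6 for m from 0 to 20%, and never more than 1.11 for ρ from 0.3 to 0.7. Changing only the motion rule gains nothing, because the ANOVA still drops a patient with one scan missing. The ratios in the lower three rows therefore require both changes.

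**The two sections side by side.** 2.12.1 assigns repeated-measures ANOVA to ROI outcomes. 2.12.5 assigns mixed models or multiple linear regression to secondary efficacy outcomes. The abstract lists ReHo and ALFF as secondary, and the Discussion includes them in the efficacy evaluation. Read literally, both sections cover them.

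**The case against.** The strongest reply is that the article separates the two analyses. Section 2.12.1 is specific to imaging, 2.12.2 covers the other indicators, and 2.12.5 concerns confounder adjustment, so an unadjusted ROI ANOVA followed by an adjusted model is a plausible reading. This softens the conflict to an ambiguity but does not remove it, since 2.12.5 makes no exception for imaging.

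A reader might infer that 2.12.5 prescribes mixed models and that 2.12.1 departs from them. The text does not support that. It offers multiple linear regression as an alternative, and ordinary regression also uses complete cases, so 2.12.5 does not guarantee that partial data are used.

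A reader might also blame the ANOVA for the patients lost to motion. That loss comes from 2.9.2.1, and replacing the ANOVA alone would not bring them back. Nor is it right that dropouts cannot be scored: their earlier scans can be measured and merely go unused.

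Three further objections stand. On dropout alone the precision cost is small. The 20% was set for FOIS in a trial with 90 days of follow-up, so fewer patients may be lost by day 30. Listwise deletion is the usual behaviour of the method, not something the article states; how missing scans are otherwise handled may be left to the full protocol or analysis plan, and that silence is not part of this point.

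**Conclusion.** The point holds as a minor improvement. The article fixes a method that, in its standard form, ignores patients without all three scans, and a second section names different methods for secondary outcomes. The participant-level motion rule is a separate weakness.

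On the plan's own dropout figure, and only if it carries over to scans by day 30, 40 of 50 per arm remain and the variance penalty is about 5-8% for correlations of 0.3 to 0.7. Penalties of about 14-18%, 24-30% and 49-61% apply only if both rules change and if motion costs 5%, 10% or 20% of scans per visit. Those rates are assumed, as are the common correlation and the timing of dropout.

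Selection is plausible given the dropout criteria in 2.5, but its size cannot be worked out from the article. It would go too far to say that a mixed model removes the bias: it reduces it only if loss is missing-at-random given the observed scans.

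**What to change.** 1. In 2.12.1, replace the repeated-measures ANOVA for ROI means with a linear mixed model (arm, visit, arm-by-visit, within-patient correlation) fitted to every usable scan.
2. In 2.12.5, name that model as the single method for the ROI outcomes, so that neither the ANOVA nor multiple linear regression remains as an alternative for them.
3. In 2.9.2.1, apply the motion limit to the affected scan rather than to the participant.

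Make changes 1 and 3 together, since most of the precision gain depends on having both. The cost is wording in three sections and an export of ROI means to SPSS, which the trial already uses and which fits such models. No new data or visits are needed. The changes should be settled before the imaging data are analysed.
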